### Sample size calculation

The required sample size to evaluate the between-group effect of the exercise-interventions (HIIT vs. ST) on the primary endpoint (proportion of Tregs in blood samples of persons with MS) in an analysis of covariance model (ANCOVA) was estimated using G*Power 3.1.9.2 [47]. The following parameters were defined for power analysis: medium effect size of d = .5, alpha of 5% and power (1-β) of 80%. As covariate in the model participants’ proportion of Tregs at baseline will be used. Sample size needed to meet the above stated suppositions can be calculated according to the formula described by Borm and colleagues [48] (1-ρ2)*n. An estimated association between participants’ baseline levels and at T1 of ρ = .7 was used. Calculation of required sample size revealed 33 participants in each group (total *N* = 66). A 10% drop-out rate was expected. This estimation was done according to the attrition rates in previous similar studies [11]. Against this background, we will recruit 72 participants in total.

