### Outcomes and assessments

#### Primary outcome

The primary outcome of this study is the change in proportions of circulating T_regs_ over the 3-week training period (T_0_ to T_3_). Blood samples will be taken by doctors or specialised nurses, via vein puncture from the antecubital vein in a seated position at T_0_ immediately before the first training session and at T_3_ after 3 weeks of training. Patients will be given 10 min between sampling and start of the exercise session to recover from any inconvenience caused by the vein puncture. All blood samples will be taken in K2 EDTA-tubes and Buffy-coat will be collected by centrifugation. Buffy-coat will be stored at − 150 °C until study completion. All samples will be analysed using flow cytometry to evaluate the proportions of T_regs_. T_regs_ will be assessed as CD3^+^CD4^+^CD25^+^ and CD127^dim^.

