### Statistics

An intention-to-treat analysis will be conducted. However, data will also be analyzed per protocol. In order to determine potential between-subjects factor effects (HIIT vs ST) at T_3_ on primary and secondary outcomes, separate univariate ANCOVAs will be used. The effects of between-subjects factor acute exercise-intervention (HIIT vs. ST), within-subjects factor measurement time-point (T1 vs. T2) and their interaction on soluble factors will be investigated with 2 × 2 mixed ANCOVAs. Covariation of participants’ levels of soluble factors at T_0_ will be considered. Post hoc Bonferroni corrected pairwise comparisons will be conducted in case of significant main effect of within-subjects factor measurement time-point. To determine if groups differ at T_1_ and/or at T_2_ simple effects analyses will be performed. ANCOVA assumptions will be explored. As measure of effect size Eta-square and Cohen’s d values, respectively, will be calculated. Finally, bivariate correlation analyses will be conducted to determine potential associations between changes in biomarkers (immune status/soluble factors) and cardiorespiratory fitness/cognitive performance/patient-reported outcomes from T_0_ to T_3_.

Statistical analyses will be performed by a statistician blinded to treatment groups coded as 1 or 2. Statistical analyses will be conducted using SPSS 25® (IBM®, Armonk, NY, USA). A result will be considered significant at *p*-value equal to or less than .05.

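### The power statement applies a correlation given for T1 to a primary analysis at T3, so its 80% is unsupported as written; separately, 72 recruits fall just short of 66 evaluable at the stated 10% drop-out

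*Protocol article*

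**What the plan says.** All of the planning figures stand in the section Sample size calculation of the protocol article. The target is the between-group effect on the proportion of Tregs, tested by ANCOVA, with "medium effect size of d = .5, alpha of 5% and power (1-β) of 80" per cent. On the covariate it says: "As covariate in the model participants’ proportion of Tregs at baseline will be used". The unadjusted sample size is multiplied by (1 − ρ²), and ρ = .7 is described as an estimated association between "baseline levels and at T1 of" .7. The result is given as: "Calculation of required sample size revealed 33 participants in each group", a total of 66. Then: "A 10% drop-out rate was expected", and "Against this background, we will recruit 72 participants in total".

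Elsewhere the article defines the endpoint and the visits:

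- **Primary outcome:** "The primary outcome of this study is the change in proportions of circulating" Tregs from T0 to T3, with blood for this outcome drawn at those two visits.
- **Statistics:** the between-group ANCOVAs for primary and secondary outcomes are at T3. T1 and T2 enter only the mixed ANCOVAs for soluble factors.
- **Abstract (Methods) and legend of Fig. 1:** T1 is immediately after the first session, and the T1 and T2 samples serve the soluble factors.
- **Immune status:** the cell counts and proportions, which include Treg numbers, are set for T0 and T3.

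**The concern.** The factor (1 − ρ²) is the share of outcome variance left after adjustment for the covariate. It applies to a given analysis only if ρ is the correlation between the covariate and the outcome in that analysis. Here that is the correlation between Tregs at T0 and Tregs at T3, about three weeks apart. The paragraph names a different pair of visits, and the second of them has no planned Treg measurement. Because this one input nearly halves the sample, the visit it refers to matters.

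The recruitment target also does not follow from the paragraph's own figures: taking 10% from 72 gives fewer than the 66 that the preceding sentences call for.

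At stake is how the primary result is read. A null finding would be judged against a claimed 80% power, so the inputs to that claim should describe the analysis that will be run.

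**Working it through.** **Inputs.** From Sample size calculation: d = .5, alpha 5%, power 80%, ρ = .7, 33 per arm (66 in total), drop-out 10%, 72 recruited. From Participants and randomization: allocation 1:1. The significance rule in Statistics ("A result will be considered significant at *p*-value equal to or less than .05") does not state sidedness. I assume two-sided, because it reproduces the plan's number and one-sided does not (51 per arm × .51 = 26.01, so 27 per arm).

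**Step 1: reproduce the plan's 66.** A two-sample t-test with d = .5, two-sided 5% and 80% power needs 64 per arm, 128 in total. The reduction factor is 1 − .7² = 1 − .49 = .51. Then 64 × .51 = 32.64, rounded up to 33 per arm, or 66. This matches exactly, so ρ = .7 is what takes 128 down to 66.

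**Step 2: check power at 66.** For ANCOVA I use the noncentral t with N − 3 degrees of freedom and noncentrality

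δ = [d / √(1 − ρ²)] × √(N/4).

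At N = 66 and ρ = .7: d / √.51 = .5 / .7141 = .7001; √(66/4) = 4.062; δ = 2.844; df = 63. Power is 80.0%. The plan's figure is correct for a T0–T3 correlation of .7.

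**Step 3: set the visits side by side.**

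| Item | Visits | Section |
|---|---|---|
| Correlation used for planning | baseline and T1 | Sample size calculation |
| Primary outcome | T0 and T3 | Primary outcome |
| Primary ANCOVA | T3 | Statistics |
| Immune cell measurements | T0 and T3 | Immune status |
| Purpose of T1 and T2 samples | soluble factors | Abstract; Fig. 1 legend |

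The planning correlation is the only item that refers to Tregs at T1.

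**Step 4: drop-out.**

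- Recruits needed for 66 evaluable: 66 / (1 − .10) = 73.3, so 74 with equal arms.
- Evaluable from 72: 72 × .9 = 64.8, so 64 to 65.
- Loss that 72 can absorb while keeping 66: 1 − 66/72 = 8.3%.
- The cruder inflation, 66 × 1.1 = 72.6, also exceeds 72.

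Power at ρ = .7 is 79.3% with 65 evaluable and 78.7% with 64, against 80.0% with 66. The cost is about one percentage point.

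**Step 5: sensitivity to ρ.** The document gives no range, so the values of ρ below are assumptions, taken on both sides of .7. Same formula, d = .5.

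| Assumed T0–T3 ρ | Power, 65 evaluable | Power, 66 evaluable |
|---|---|---|
| .5 | 63% | 64% |
| .6 | 70% | 71% |
| .7 | 79% | 80% |
| .75 | 85% | 86% |

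**The case against.** The strongest reply is that T1 is a slip for the post-intervention visit. The sentence sits inside a calculation for the primary endpoint with baseline Tregs as covariate, and no T1 Treg measurement is planned. On that reading .7 is the T0–T3 value and the calculation stands. This is plausible, and it is why the 80% is unsupported as written and not disproved. It does not remove the need for correction, because T1 is a defined visit throughout the article and Statistics uses it in its own right.

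Three stronger inferences may tempt a reader; the document supports none of them.

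- *Power is shown to be lost because a same-day correlation must exceed a three-week one.* The article gives no data on either correlation. T1 is sampled right after an exercise stimulus, so greater stability at T1 cannot be presumed.
- *The exclusions listed under Participants and randomization add to the 10%.* Withdrawal of consent is ordinary drop-out, and nothing places severe relapse or medication on the test day outside the 10%, which was taken from attrition in similar studies.
- *80% holds only if ρ is exactly .7 and losses stay under 8.3%.* A somewhat higher ρ compensates: with 64 evaluable, ρ = .72 gives 81%.

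It is also fair to say that ρ is one planning assumption among others. At 66 evaluable and ρ = .7, power is 61% for d = .4 and 92% for d = .6. A condensed article may leave the source of .7 to the full protocol, so its absence is not part of this point. Lastly, a shortfall of two recruits lies within ordinary tolerance. That is accepted, and it is treated here as minor.

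**Conclusion.** The point holds in limited form. The input that nearly halves the sample is stated for a visit at which the primary outcome is not planned to be measured, so the power claim does not, as written, describe the T3 comparison. Whether true power is above or below 80% cannot be settled from the document; it depends on the T0–T3 Treg correlation. The recruitment figure is a separate and minor error: 72 where 74 follows from the stated inputs, leaving about 79% power at ρ = .7.

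These conclusions rest on a two-sided 5% test, d = .5, equal arms and, for the sensitivity figures, an assumed range of ρ. The correction is worth making because this is the power statement for the primary outcome.

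**What to change.** In Sample size calculation:

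1. Replace the reference to T1 with T3, and describe .7 as the assumed correlation between Treg proportions at T0 and T3.
2. State that 72 recruited, less 10%, gives 64 to 65 evaluable and about 79% power at that correlation.
3. Add a line showing power over assumed correlations on both sides of .7, for example at 65 evaluable: 63% at .5, 70% at .6, 79% at .7 and 85% at .75. Label the range as an assumption.

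This changes wording only. Design, analysis and recruitment target stay as they are, and no extra participants are required. The cost is a stated power slightly less favourable than 80%.

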### Statistics

An intention-to-treat analysis will be conducted. However, data will also be analyzed per protocol. In order to determine potential between-subjects factor effects (HIIT vs ST) at T_3_ on primary and secondary outcomes, separate univariate ANCOVAs will be used. The effects of between-subjects factor acute exercise-intervention (HIIT vs. ST), within-subjects factor measurement time-point (T1 vs. T2) and their interaction on soluble factors will be investigated with 2 × 2 mixed ANCOVAs. Covariation of participants’ levels of soluble factors at T_0_ will be considered. Post hoc Bonferroni corrected pairwise comparisons will be conducted in case of significant main effect of within-subjects factor measurement time-point. To determine if groups differ at T_1_ and/or at T_2_ simple effects analyses will be performed. ANCOVA assumptions will be explored. As measure of effect size Eta-square and Cohen’s d values, respectively, will be calculated. Finally, bivariate correlation analyses will be conducted to determine potential associations between changes in biomarkers (immune status/soluble factors) and cardiorespiratory fitness/cognitive performance/patient-reported outcomes from T_0_ to T_3_.

Statistical analyses will be performed by a statistician blinded to treatment groups coded as 1 or 2. Statistical analyses will be conducted using SPSS 25® (IBM®, Armonk, NY, USA). A result will be considered significant at *p*-value equal to or less than .05.

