### Participants and randomization

Participants will be consecutively recruited on the day of admission for inpatient rehabilitation in the Valens Rehabilitation Center (Switzerland). They will be screened for study inclusion during a 12-month period. Key inclusion criterion for the participants’ eligibility will be a definite MS diagnosis (according to the revised McDonald criteria [32]) with relapsing remitting or secondary progressive MS phenotype and an Expanded Disability Status Scale (EDSS) [33] score between 3.0 and 6.0 (inclusive). Participants will be excluded if they experience acute severe relapses during the 3-week study, are given immune-modulating medication the day of CPET at baseline or T_3_, or withdraw their consent to participate. Detailed information for in- and exclusion criteria are shown in Table 1.

**Table 1 Tab1:** In- and exclusion criteria

INCLUSION	EXCLUSION
• *Relapsing remitting* or *secondary progressive MS*	• Pregnant or breast feeding women
• *EDSS: 3.0 – 6.0*	• Women planning to become pregnant during study period
• *Age > 21 years*	• Concomitant diseases (internistic, neurological or orthopaedic) limiting the execution of the intervention and assessments or affecting study endpoints
• Informed *consent* as documented by signature	• Drug or alcohol abuse
	• Problems of understanding (not German-speaking), psychological disorders, dementia etc. affecting the ability to understand study course and execute study instructions
	• Persons who already participated in the current study
	• Enrolment of persons employed for study execution, family members of the investigator and himself
	• Acute melanoma and cancer diseases under treatment of chemotherapy or radiation therapy

Participants will be randomly allocated (1:1) to one of the two training programs. Randomization will be conducted using “Randomization-In-Treatment-Arms” software (RITA, Evident, Germany). Randomization will follow the minimization procedure according to Pocock and Simon (for review see Scott et al. [34]) using disease severity (EDSS score), fatigue, age and level of cardiorespiratory fitness as factors for stratification.

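### Allocation is minimised on EDSS, fatigue, age and fitness, but no model is stated to include these factors; adding them to the T3 ANCOVAs is a cheap improvement

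*Protocol article*

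**What the plan says.** Under Participants and randomization, allocation is 1:1 and "Randomization will follow the minimization procedure according to Pocock and Simon", "using disease severity (EDSS score), fatigue, age and level of cardiorespiratory fitness as factors for stratification". The assignment probability and the cut-points are not given.

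Under Sample size calculation, the primary model is an ANCOVA for the between-group effect on Tregs: "As covariate in the model participants’ proportion of Tregs at baseline will be used". The trial is sized on that one covariate, with an assumed correlation of 0.7 between baseline and follow-up.

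Under Statistics, the T3 analysis is described by "on primary and secondary outcomes, separate univariate ANCOVAs will be used". For the acute models at T1 and T2 the text adds "Covariation of participants’ levels of soluble factors at T_0_ will be considered". Neither sentence mentions a minimisation factor. For the secondary T3 outcomes the covariate is not written out; adjustment for the outcome's own baseline is the natural reading, but it is an inference.

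**The concern.** Minimisation keeps the arms similar on the chosen factors, so chance imbalance in them contributes less to the treatment difference than it would under simple randomisation. A model that leaves the factors out still counts their variation as error. If the factors are prognostic, the reported standard error then overstates the real variability of the estimate. The test rejects less often than its nominal 5% under the null, and precision that the allocation has bought goes unused. In a trial sized at 66 evaluable participants, that precision is worth having. The usual principle is to analyse by what the trial allocates by, and here the two do not match.

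**Working it through.** **Inputs.** From the article: d = 0.5, alpha 5%, power 80%, ρ = 0.7, 33 per arm, four minimisation factors, 1:1 allocation. Not in the article, so assumed: R², the share of the residual variance (after baseline Tregs) that the four factors explain, taken from 0 to 0.30; the assignment probability, 0.8 or 1.0; factors split at the median, independent of each other and of baseline Tregs, with linear effects.

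**The plan's own figure.** A two-sided two-sample comparison at d = 0.5 needs 63 per arm (normal approximation) or 64 (t-test). The variance factor is 1 − 0.7² = 0.51. Then 0.51 × 63 = 32.1 and 0.51 × 64 = 32.6, both rounding up to 33 per arm, 66 in total. The stated figure is reproduced. At 33 per arm the noncentrality is 0.5 / (√0.51 × √(2/33)) = 2.84 on 66 − 3 = 63 degrees of freedom, and power is 80.0%. So the baseline-only model delivers what was planned.

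**Size of the conservatism.** If the arms were perfectly balanced on the factors, the true standard error would be √(1 − R²) times the one the model reports. The type I error would then be 2 × [1 − Φ(1.96 / √(1 − R²))]: 4.4% at R² = 0.05, 3.9% at 0.10, 2.8% at 0.20 and 1.9% at 0.30. Real minimisation works on categories and leaves some imbalance, so the actual effect is milder.

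**Simulation.** N = 66, Pocock-Simon minimisation, 4,000 trials per cell, Monte Carlo error about 0.3 points for type I error and 0.6 for power. Each cell gives the result for assignment probability 0.8 / 1.0, in per cent. The factors enter as continuous covariates.

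| Assumed R² | Type I, baseline only | Type I, factors added | Power, baseline only | Power, factors added |
|---|---|---|---|---|
| 0 | 4.8 / 5.9 | 4.6 / 5.7 | 79.8 / 80.4 | 78.5 / 78.8 |
| 0.05 | 4.7 / 5.0 | 5.1 / 5.5 | 80.5 / 79.6 | 80.1 / 80.3 |
| 0.10 | 4.2 / 4.5 | 4.5 / 4.9 | 79.9 / 79.7 | 83.0 / 81.5 |
| 0.20 | 4.1 / 3.7 | 5.3 / 4.7 | 80.6 / 80.7 | 86.5 / 86.6 |
| 0.30 | 3.2 / 2.9 | 5.2 / 4.7 | 81.4 / 82.1 | 90.5 / 91.3 |

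The 5.9% at R² = 0 is simulation noise: with non-prognostic factors and normal errors the test is exact at 5%.

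A separate simulation with 8,000 to 10,000 trials per setting agrees. At R² = 0.10, 0.20 and 0.30, with the factors omitted, type I error was 4.5%, 3.9% and 3.7% and power 79%, 81% and 81%. With them included, power was 81%, 86% and 90%.

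**Cost when the factors are not prognostic.** With four more covariates the degrees of freedom fall from 63 to 59. Power falls from 80.0% to 79.9% if the arms are exactly balanced, and by 1.3 to 1.6 points in simulation, where some imbalance remains.

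**Factors entered as categories.** Entering the median-split categories instead of continuous values also restores the type I error (4.7% to 5.5% for R² of 0.10 to 0.30), but gains less power: 81% to 87% over the same range.

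**The case against.** The strongest objection is that the effect is conditional on a quantity the article does not supply. Baseline Tregs are already assumed to explain 49% of the variance (0.7²). The Background links fitness to circulating Tregs as a general finding, not one in MS, and baseline Tregs would carry much of such a standing association. Nothing in the article links EDSS, age or the fatigue score to Tregs. At R² = 0.05 adding the factors gains nothing measurable. All of this stands, and it limits the claim.

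Three stronger readings are tempting, and the documents do not support them:

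- That the type I error is below 5% as a matter of fact. It is so only if R² is appreciable.
- That planned power is lost. The 33 per arm was calculated for the baseline-only model and reproduces at 80%; only additional power is forgone.
- That adjustment is free. It uses degrees of freedom and can cost up to about 1.5 points of power.

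It may also be said that covariate lists belong in an analysis plan that is not shown. That has force for the secondary outcomes, where the covariate is not written out. It has less force for the primary outcome, where the article names the covariate and sizes the trial on it, although it does not say that no other will be used.

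A practical objection is that the Cardiorespiratory fitness section defines VO2peak by criteria that some participants may not reach, so a model requiring it could lose participants. That affects how the fix is worded, not whether it is worth making.

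**Conclusion.** The mismatch between allocation and stated analysis is real for the primary outcome and likely for the secondary T3 outcomes. Its direction is conservative: it does not inflate false positives, and it does not undermine the planned 80% power. Its size turns on the unstated R²: negligible at 0 to 5%; at 10 to 30%, the type I error is about 4.5% to 3% and some 2 to 9 points of power are left unused. These figures rest on the simulation assumptions listed above, in particular median splits and independent factors. For fatigue and fitness as outcomes, one factor is already in the model if the outcome's baseline is the covariate. This is a cheap improvement, not a threat to validity.

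**What to change.** State that the primary T3 ANCOVA includes EDSS, fatigue score, age and cardiorespiratory fitness, as recorded before allocation, next to baseline Tregs, and that each secondary T3 ANCOVA includes them next to the outcome's baseline value. For fitness, use the value that entered the minimisation; every allocated participant should have one, so nobody is dropped for a missing covariate. Continuous values are preferable where available, because they recover more power. Where a factor is itself the outcome, it is already in the model as the baseline.

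The change takes one sentence and needs no new data, visits or participants. It uses up to four degrees of freedom (more only if a factor is entered in more than two categories). It should be fixed before the groups are compared, so that the choice of adjustment cannot depend on the results.

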## Methods/design

A two-armed single-blind randomized controlled trial design will be adopted. Prior to inclusion, participants will be asked to provide written informed consent. Participants will be randomized into two different training groups performing either high-intensive interval (HIIT), or moderate continuous (ST) aerobic exercise training on a bicycle ergometer over a period of 3 weeks. Both groups will be assessed on the cardiopulmonary exercise test (CPET) before and after the intervention period. The training performed within both groups will be supervised by independent physiotherapists who will be blind to all other study assessments. The principal investigator will complete CPET and data analysis blinded to the training condition. Participants will not be blinded regarding their individual training intensity. The study design will contain four measurement time-points, considering both acute and chronic effects of each exercise training modality (see Fig. 1). All outcome parameters will be assessed at baseline within a period of 48 h before the first exercise session (T_0_) and at the end of the 3-week exercise training intervention, 48 h following the last training session (T_3_). Blood samples at baseline (T_0_) will be taken immediately before the first exercise session. Outcome changes between T_0_ and T_3_ will indicate the effects of chronic exercise training. Additionally, blood samples will be taken immediately after completion of the first exercise session (T_1_) and 3 h after completion of the first exercise session (T_2_) to provide further information on the acute effects of different exercise modalities on (anti-) inflammatory factors, TRP metabolites and BBB markers. The measurement time point T_2_ is implemented in the study design to examine the kinetics of soluble factors in response to a single-bout of exercise.

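### If run as a classical repeated-measures model, the acute 2 × 2 mixed ANCOVA drops anyone missing T1 or T2; a linear mixed model would keep the observed values (minor, secondary outcomes only)

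*Protocol article*

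**What the plan says.** The Methods/design section sets four time-points. Blood is drawn before the first session (T0), immediately after it (T1), three hours after it (T2), and after three weeks (T3). The Soluble factors section lists twelve analytes measured at all four.

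The Statistics section fixes the acute model. The between-subjects factor is arm (HIIT, ST), the within-subjects factor is time-point with two levels (T1, T2), and "their interaction on soluble factors will be investigated with 2 × 2 mixed ANCOVAs". Baseline enters as a covariate: "levels of soluble factors at T_0_ will be considered". Contrasts between arms at each time-point follow: "To determine if groups differ at T_1_ and/or at T_2_ simple effects analyses will be performed".

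On population and software, the same section says: "An intention-to-treat analysis will be conducted. However, data will also be analyzed per protocol", and "Statistical analyses will be conducted using SPSS 25". It does not name the SPSS procedure, and it does not say how a participant with only one of the two post-exercise values is treated.

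**The concern.** Within- and between-subjects factors, Bonferroni-corrected pairwise comparisons, simple effects and Eta-square are the vocabulary of the classical repeated-measures general linear model. That model treats T1 and T2 as a pair and needs both, plus T0. A missing T2 value therefore removes a valid T1 value for that analyte, and the reverse.

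T1 is taken on the ergometer during cool-down and T2 is a separate draw three hours later, so either can fail alone. The analytes are assayed separately (ELISA or chromatography), so the analysed set could also differ from one factor to the next.

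Two things are at stake. One is precision: the T1 contrast would depend on whether a later sample exists. The other is bias: if participants who miss T2 differ in their acute response, the complete pairs are a selected group at both time-points. The outcomes are secondary, but this is the only planned analysis of the acute half of the objective in the abstract.

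**Working it through.** **Inputs from the protocol article.** Sample size calculation: d = .5, alpha 5%, power 80%, ρ = .7, 33 per group, 66 in total, 10% drop-out, 72 recruited. Allocation is 1:1 (Participants and randomization).

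**Assumptions.** Two-sided testing. d = .5 and ρ = .7 are given for the Treg endpoint and borrowed here for the soluble factors. T2 missing rates of 5%, 10% and 20% are illustrative.

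**Step 1: the plan's own figure.** A two-sample t-test with d = .5, two-sided 5% and 80% power needs 64 per group. The ANCOVA reduction is 1 − ρ² = 1 − .49 = .51, and 64 × .51 = 32.64, rounded up to 33 per group, or 66. This matches. No power is stated for the acute analysis.

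**Step 2: which base to use.** The 66 is the number left after the three-week drop-out allowance. T1 and T2 fall at the first session, before most of that drop-out can occur. The base is therefore 72, or 36 per arm.

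**Step 3: power for the T1 contrast if T2 is missing completely at random.** The standardised effect after baseline adjustment is .5 / √.51 = .700. With a share m missing, n = 36(1 − m) per arm, noncentrality = .700 × √(n/2), and df = 2n − 3. The standard error grows by 1/√(1 − m).

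| T2 missing | n per arm | Noncentrality | Power, complete pairs | SE inflation |
|---|---|---|---|---|
| 0% | 36.0 | 2.97 | 83.4% | none |
| 5% | 34.2 | 2.90 | 81.4% | 2.6% |
| 10% | 32.4 | 2.82 | 79.2% | 5.4% |
| 20% | 28.8 | 2.66 | 74.2% | 11.8% |

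Keeping every observed T1 value leaves power at 83.4% in each row.

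**Step 4: simulation.** 4,000 trials of 72 participants were generated per scenario, with a true effect of .5 at T1 and T2 and all correlations .7.

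- *10% of T2 missing completely at random.* The T1 estimate is .50 with complete pairs and .50 with all T1 values. Power is 78.2% against 82.3%, the same four-point loss as in the table.
- *Response-related missingness, deliberately strong.* T2 is missing in 10% overall, all in the HIIT arm (so about 20% of that arm), and is more likely the higher the T1 value. Complete pairs give .37 at T1 and .45 at T2. An analysis that uses all observed values gives .49 and .50.

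**The case against.** The strongest reply is that the article names a model family and states no complete-case rule. A reader might infer that T1 values will certainly be discarded and that the plan contradicts its own intention-to-treat statement. The documents do not support that. No SPSS procedure is named, and no sentence excludes participants with partial data. If the simple effects are run as separate ANCOVAs at T1 and at T2, every T1 value is kept. Handling of missing data is also commonly left to the analysis plan, which is not shown. All of this stands, so the point has to be conditional.

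It does not remove the point, because the natural reading of the named model is the classical one, and that model has this deletion property. Separate ANCOVAs would be only a partial answer: the test of arm by time still needs pairs, and a T2-only ANCOVA still gives .45 in the response-related scenario.

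A reader might also infer that T2 will often be missing and that the contrasts will be pulled toward no difference. The documents give no grounds for either. Participants are inpatients, T2 is on the same day, and the 10% drop-out figure belongs to the three-week primary endpoint. Plasma is stored until the end of the study, so the analyte values cannot be known when T2 is drawn. A link could arise only indirectly, for example through how the participant feels, and nothing shows how strong it would be.

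Finally, power figures that start from 33 per arm look worse (about 80% falling to 75.5% at 10% missing) but subtract losses from a number already net of drop-out.

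**Conclusion.** The concern holds conditionally, as a minor point. Run as the classical model its wording describes, the acute analysis drops incomplete pairs, loses observed data and fits poorly with the stated intention-to-treat analysis.

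The illustrated cost to T1 power is about 2 points at 5% missing T2, 4 points at 10% and 9 points at 20%, from a base of about 83%. These figures rest on the borrowed d and ρ and on assumed missing rates. Bias is zero under missingness completely at random. It is also zero if missingness depends only on arm and T0 and the model is correctly specified. It arises when missingness depends on the acute response, and the simulated fall to .37 shows that this is possible, not that it is expected.

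Only secondary outcomes are affected. The primary Treg comparison at T3 is a separate univariate ANCOVA and is untouched.

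**What to change.** Specify one linear mixed model per soluble factor, fitted by REML, with an unstructured within-person covariance for T1 and T2 and with arm, time, arm × time, T0 and T0 × time as fixed effects. Include every randomised participant with T0 and at least one of T1 and T2. Take the HIIT–ST contrasts at T1 and at T2 from this model. State this before unblinding, so that the procedure is not chosen after the data are seen.

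The cost is a change of wording. The MIXED procedure is part of the software already named, and with complete data the model gives the same group contrasts as the planned analysis. The downside is reliance on a missing-at-random assumption. That is weaker than what complete pairs need, but the model would not remove bias if missingness depended on the unseen T2 value itself.
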